#### Pain progression and opiate use

Pain and analgesic management using opiates will be assessed using the Brief Pain Inventory Short Form (BPI-SF) [35] and a review of medical records at baseline, 12 and 24 weeks. The BPI was originally developed to assess pain severity and impact in cancer patients, with reported good internal consistency and validity [36, 37]. The BPI-SF is now widely recommended as a core outcome measure in clinical trials.

#### Skeletal-related events

Symptomatic skeletal-related events (SSEs) will be determined at treatment clinics and reviewing patient medical records, continuously throughout the 24-week intervention.

#### Fatigue and QOL measures

Cancer-related fatigue will be determined using the FACIT fatigue scale at baseline, 12 and 24 weeks [38]. The Functional Assessment of Cancer Therapy—Prostate (FACT-P) and EuroQOL five-dimensional questionnaire (EQ-5D-5 L) will be measured at the same time points to assess QOL. Both questionnaires are internationally recognised validated measures for all stages of prostate cancer and are sensitive to changes in indicators of treatment efficacy [39–41]. The change in score for the FACT-P and FACIT fatigue questionnaires can be calculated for each participant and categorised according to pre-established minimally important differences (MIDs). The EQ-5D-5 L will be used as a general index of health status and to inform the cost-effectiveness of future trials across the five dimensions.

#### Physical activity levels

Each patient’s level of physical activity will be assessed subjectively at baseline, 12 and 24 weeks using the International Physical Activity Questionnaire Short Form (IPAQ-SF). Craig et al. [42] reported the IPAQ-SF produced repeatable data and has acceptable measurement properties for self-report physical activity. Lee and colleagues [43] have reported the IPAQ-SF typically overestimates physical activity and thus should be supplemented with objective measures. In order to prevent this potential overestimation, this questionnaire will be completed in consultation with an Exercise Physiologist. Further, to complement the subjective assessment, objective physical activity will be captured the week prior to each outcome visit, using an accelerometer (ActiGraph GT3X). The accelerometer will be worn for 7 days, capturing data at 10-s Epoch intervals. The analysis will be completed at 60-s Epoch intervals, in accordance with recommendations [44, 45]. Moderate to vigorous physical activity and step counts will be assessed for each patient.

#### Physical fitness

Physical fitness will be assessed at baseline, 12 and 24 weeks using a timed sit-to-stand test (30 s) and 6-min walking test. The number of repetitions will be recorded during the sit-to-stand test, while the distance covered will determine aerobic fitness.

### Qualitative evaluation

Upon study completion (week 24), the impact and experiences of key stakeholders including active participants, eligible patients that declined participation and the research staff delivering the intervention will be collected, via face-to-face semi-structured interview. Men who declined to participate will be given the opportunity to discuss their decision and gather information on suitable alternatives. Study staff interviews will be conducted by an impartial colleague to reduce bias.

The feasibility, acceptability, potential utility of the program, approaches to optimise and appropriateness of the timing and outcome measures will be a priority during interviewing. The semi-structured interviews will explore perceived facilitators and barriers to exercise and experiences of exercise in managing treatment-related symptoms, with common themes extracted during content analysis. Information relating to the number screened and eligible, retention and compliance, follow-up rates and satisfaction will be recorded on a discussed weekly but revisited during interviewing, followed by a descriptive analysis. Interviews will be tape-recorded and transcribed verbatim.

### Ethical approval

Ethical approval to conduct this study was obtained from the Office for Research Ethics Committees Northern Ireland (ORECNI) in 2018 (IRAS project ID: 248301). Any subsequent protocol modifications will be reviewed by ORECNI. Following approval, a memorandum, detailing the amendment, will be issued to all members of the trial steering committee.

### Data management and monitoring

All data collected will be stored securely in accordance with General Data Protection Regulations (within a key card accessed building, on a password-protected computer and locked filing cabinet). Only members of the study management team will have access to this data. A trial steering committee (comprising [name] and NICRCF advisory group members) will oversee the trial and convene regularly to discuss pertinent aspects of the study. As clinical oncologists sit on this trial steering committee, we felt a trial data monitoring committee was not required. Spontaneous adverse events will be captured during regular, weekly contact with patients. Any adverse events will be expedited to the trial oncologists, upon report, for an immediate resolution and further reviewed at regular committee meetings. This trial will be subject to audit from the study sponsor, who has the power to terminate the trial if necessary. Trial results will be submitted for publication and communicated in a relevant medical or scientific journal. Anonymity will be maintained and unique identifiers will be removed in any subsequent outputs.

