### Study objectives

The primary objective of this study is to establish the feasibility of delivering a prescribed exercise intervention to men with advanced prostate cancer, who are ineligible for high-intensity exercise (i.e. the Movember GAP4 INTERVAL study). As part of this primary objective, we will collect data:
To determine patient eligibility and recruitment rates.To assess adherence to the programme and attrition rates.To determine the rate of exercise-induced adverse events (if any).To ascertain the extent to which the intervention might be integrated into clinical practice (and the cost implications of doing so).To refine methodological variables, optimising the study design and data collection processes.To explore the perceptions, acceptability and experiences of men with advanced prostate cancer undertaking the intervention and those men eligible that declined participation.To explore the perception and experience of those recruiting to and/or delivering the intervention (e.g. Exercise Physiologist/Clinical Oncologists/Research Nurses).

Secondary objectives will focus on the feasibility of data collection processes, mainly collecting changes in body composition, functional ability, physical fitness, physical activity levels and patient-reported outcome measures (cancer-related fatigue, pain and quality of life). Additionally, we will use this feasibility trial to collect preliminary data on health resource usage to inform cost-effectiveness of future trials and refine statistical considerations (e.g. ascertain sample size estimates).

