### Behavioural support

The behaviour change component of this particular programme is based on the COM-B method [34]. Behavioural support will comprise a behavioural change consultation at baseline and weekly, structured telephone contact. The behavioural support component will follow a scripted protocol of defined questioning, to maintain intervention fidelity. The same member of the research team will lead the behavioural consultations throughout, to maintain reliability. Information pertaining to weekly exercise adherence, perceived barriers and potential solutions, weekly goal setting and self-confidence will be recorded. Behavioural support sessions provide the opportunity to reinforce key aspects of the trial and a chance to provide positive feedback on progress. Records of call durations and patient availability will be stored. The behavioural support programme will ensure continuity in the exercise prescribed, so all patients receive equal support to meet the desired exercise volume by study cessation. The purpose of this communication is to maintain a close relationship with the patient and identify additional support required. Accurate recording of physical activity data is essential to enable associations with treatment-related adversities and the outcome markers. Participants will specify their preferred communication type (if not telephone), to ensure regular contact is maintained.

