### Primary endpoint

The primary endpoint is to determine the feasibility of delivering a tailored, home-based, 12-week exercise intervention in men with metastatic castrate-resistant prostate cancer. Recruitment and attrition rates, exercise adherence (number of sessions completed), general safety/adverse events and the patient experience will be a focus of determining feasibility.

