### Secondary endpoints

Secondary endpoints will be assessed at baseline, 12 and 24 weeks accounting for pain, cancer-related fatigue, skeletal-related events, physical fitness and QOL. Direct contact throughout the study will also serve as a feedback loop for certain measures should they occur outside each visit. Secondary outcome measures will be assessed mainly for completeness in accordance with the feasibility theme of the study. Although the sample size is small and perhaps underpowered to definitely report causation, changes from baseline will be analysed, to provide an indication of efficacy and detect any differences. It should be noted that all secondary outcome measures are obtained principally for testing the ability to undertake and complete measures and not to detect differences from baseline. Processes relating to data handling and analysis are described in greater detail in the “Data analysis” section.

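### Non-skeletal exercise-related adverse events in weeks 1–12 have no stated elicitation method beyond spontaneous capture at the weekly call, so their rate, part of the primary objective, may be under-counted

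*Protocol article*

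**What the plan says.** All references are to the protocol article.

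- **Study objectives** lists, among the data to be collected for the primary objective: "To determine the rate of exercise-induced adverse events (if any").
- **Primary endpoint** states that "general safety/adverse events and the patient experience will be a focus of determining feasibility".
- **Data management and monitoring** gives the method: "Spontaneous adverse events will be captured during regular, weekly contact with patients". Reported events then go to the trial oncologists.
- **Behavioural support** describes the weekly contact: "The behavioural support component will follow a scripted protocol of defined questioning, to maintain intervention fidelity". On content it says: "Information pertaining to weekly exercise adherence, perceived barriers and potential solutions, weekly goal setting and self-confidence will be recorded". One team member leads these consultations throughout.
- **Skeletal-related events** gives a second route. Symptomatic skeletal events "will be determined at treatment clinics and reviewing patient medical records, continuously throughout the 24-week intervention".
- **Secondary endpoints** adds: "Direct contact throughout the study will also serve as a feedback loop for certain measures should they occur outside each visit".
- **Pain progression and opiate use** schedules the BPI-SF and "a review of medical records at baseline, 12 and 24 weeks".
- **Table 3** marks safety/adverse events at weeks 1–12 and week 25, and medical history at weeks 1–12 among other times.
- **Data analysis** says the interviews will also inform safety. **Qualitative evaluation** places them at week 24.

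**The concern.** A rate needs a numerator obtained in the same way from every participant. If events enter the record only when a man mentions them, the numerator depends on how forthcoming he is, and on what he thinks the caller wants to hear. Here the caller is the person encouraging him to exercise. The contact exists to support adherence, and the listed items centre on adherence, barriers, goals and confidence. A symptom that led to a missed session could be noted as a barrier without also being recorded as an event.

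The setting raises the stakes. The Discussion explains that supervised exercise is usually advocated in this population because of fracture risk, whereas this programme is unsupervised at home. The example prescription in Table 4 steps up almost weekly until week 10. Data management and monitoring says no separate data monitoring committee was thought necessary, and referral to the oncologists begins when an event is reported. Any loss of events would make the programme look safer than it is. The rate would then be carried into the design of the planned randomised trial.

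**Working it through.** **Step 1. Which stated route would find which event in weeks 1–12?**

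| Route | Skeletal events | Fall without fracture, muscle or joint injury, pain flare |
|---|---|---|
| Treatment clinics and medical records (Skeletal-related events) | Yes, continuous | Not stated |
| Weekly contact (Data management and monitoring) | Spontaneous | Spontaneous |
| Listed call items (Behavioural support) | No item listed | No item listed |
| Feedback loop (Secondary endpoints) | Unnamed measures | Unnamed measures; no method of asking |
| Table 3, safety and medical history | Says when, not how | Says when, not how |
| BPI-SF and records | Baseline, 12, 24 weeks | Pain only, at the same three times |
| Interviews | Week 24, retrospective | Week 24, about 24 − 12 = 12 weeks after the programme ends |

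Skeletal events have a route that does not depend on a man volunteering anything. For the other events, the only in-programme method stated is spontaneous capture at the weekly contact.

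**Step 2. Is there a figure to reproduce?** The article states no expected adverse event rate and no capture share. The amount of under-counting therefore cannot be derived from it.

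**Step 3. What incomplete capture would do, under assumptions.**

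Inputs:
- n = 30 men (Sample size calculation).
- p = true proportion of men with a non-skeletal exercise-related event. Assumed: 5%, 10% or 20%.
- s = share of those men whose event is captured. Assumed: 100%, 75%, 50% or 25%.

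Formulas: expected number recorded = 30 × p × s; chance of recording none = (1 − p × s)^30.

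| p | s = 100% | s = 75% | s = 50% | s = 25% |
|---|---|---|---|---|
| 5% | 1.5 men; 21% | 1.1; 32% | 0.75; 47% | 0.4; 69% |
| 10% | 3.0 men; 4% | 2.25; 10% | 1.5; 21% | 0.75; 47% |
| 20% | 6.0 men; 0.1% | 4.5; 0.8% | 3.0; 4% | 1.5; 21% |

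Each cell gives the expected number of men recorded and the chance of recording none. For example, with p = 10% and s = 50%: 30 × 0.10 × 0.50 = 1.5 men, and 0.95^30 = 0.21.

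**Step 4. Effect on interpreting a clean result.** With no events in 30 men, the exact two-sided 95% upper limit is 1 − 0.025^(1/30) = 11.6%. That limit applies to the rate of *captured* events and equals a limit on the true rate only if s = 100%. If s were 75%, the limit on the true rate would be 11.6% / 0.75 = 15.4%. If s were 50%, it would be 11.6% / 0.50 = 23.1%.

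**The case against.** The strongest reply has four parts.

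1. *Capture is not confined to the call.* This stands for skeletal events, the harm the article treats as central. A reader might infer that volunteered reports are the sole source of safety data during the programme. The Skeletal-related events section rules that out, and Table 3 schedules safety and medical history in weeks 1–12. None of these routes, however, is described as asking about falls without fracture, soft-tissue injury or pain flares.

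2. *The call script is not shown, and a condensed article may leave its wording to a fuller document.* This stands in part. The list of call items is not exhaustive: the same section mentions other records, and one stated purpose of the contact is to spot further support needs. Absence from the list does not prove that no symptom question is asked. The point nevertheless rests on a method the article does state, spontaneous capture, for a rate it places under the primary objective.

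3. *The adjective qualifies the events, not the reporting.* It could mean events arising unexpectedly between visits rather than unprompted reports. The ambiguity is real. On either reading, the two sections together do not say whether every man is asked.

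4. *The decision is not affected.* Progression criteria rest on recruitment and, secondarily, adherence, with no adverse event threshold. This stands, so the point does not change the stated progression rule. The event rate is still something the trial undertakes to deliver, and it bears on whether unsupervised exercise can be called safe in these men.

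**Conclusion.** The point holds for non-skeletal events in weeks 1–12, as a risk of under-counting. It should be addressed but does not undermine the trial. For these events the article states one in-programme method, and the description of the contact that carries it lists no relevant question.

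A reader might go further and conclude that the exercise-induced event rate *is* under-counted, or that a particular fraction will be missed. The document does not support that. The script is unseen, the key word is ambiguous, and every figure in the tabulation that depends on a true rate or a capture share rests on an assumed value. The direction is clear, since incomplete capture can only lower the recorded rate. The size is unknown. Nor is a delay in referral to the oncologists demonstrated; the text shows only that referral begins with a report.

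**What to change.** In Data management and monitoring, replace spontaneous-only capture with elicited capture at the existing weekly contact, and add the matching items to the list in Behavioural support:

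- Ask every man the same short set of questions at each contact: any fall, injury, or new or worse pain since the last contact; the date; and its relation to exercise.
- Ask whether any missed session was due to a symptom, so that a barrier can also be recorded as an event.
- Log positive answers as adverse events through the existing reporting route.
- Report solicited and volunteered events separately, and state the date on which the script changed. Trial status records seven men entered at submission, so up to 30 − 7 = 23 of the planned 30 could be followed under the revised script from the start.

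If the script already contains such questions, correcting the word *Spontaneous* and saying so is enough. If elicitation is not adopted, report the non-skeletal rate as a lower bound.

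Cost: about one to two minutes per call over 30 × 12 = 360 planned weekly contacts, or roughly 6 to 12 hours in total, with no new visits or staff. The downside is that more minor events will be recorded, so the stated rate will look less favourable.

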### Data analysis

From a feasibility perspective, data analysis will account for the number of patients screened, numbers participating in the intervention and the numbers unwilling to participate, after eligibility is confirmed, with reasons for non-participation. This data will be examined and scrutinised using descriptive analysis to identify differences between participants and non-participants. Patient compliance, utilisation and satisfaction with the intervention will be assessed, as will completion rates for the intervention and the outcome measures. The acceptability of the physical outcome measures and questionnaires used in determining health resource use will also be reported. Additionally, the feasibility of the accelerometer data (e.g. volume and quality) will be analysed. All measures will be scored according to standard practice and analysed for mean changes from baseline, using a one-way repeated measures ANOVA. For each outcome measure, change will be calculated as follow-up (at both 12 and 24 weeks) minus baseline and presented alongside 95% CIs. We will also calculate effect size (Cohen’s *d*) for each outcome measure, at 12 and 24 weeks, using the following formula: (mean post-test − mean baseline)/(baseline standard deviation). Conventions of small (*d* = 0.20), medium (*d* = 0.50) and large (*d* = 0.80) will be used. Preliminary feasibility results will inform the future RCT sample size calculation and the parameters for investigation to determine potential clinical meaningfulness.

Transcriptions of audio recorded interviews will be analysed using thematic analysis [46]. At each stage, findings will be verified and discussed in order to assess the accuracy of the interpretation, promote reliability and ensure rigour [47]. NVivo qualitative data analysis software will be used to aid data management. Data generated from interviewing will assist in determining the safety of the intervention as well as the health economics moving forward.

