### Sample size calculation

As this is a feasibility study, a formal sample size calculation has not been performed. We aim to recruit 30 patients to the study which is standard practice for feasibility trials [31–33]. Assuming an 80% adherence rate, 25 patients should complete the intervention and subsequent evaluation.

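### The named one-way repeated-measures ANOVA discards partial data from men who miss a visit, and the effect-size formula does not fix a common set of men; a mixed model and one defining sentence would repair both.

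*Protocol article*

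**What the plan says.** All of this is in the protocol article.

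- **Method (Data analysis).** "All measures will be scored according to standard practice and analysed for mean changes from baseline, using a one-way repeated measures ANOVA".
- **Visits (Secondary endpoints).** "Secondary endpoints will be assessed at baseline, 12 and 24 weeks".
- **Change scores (Data analysis, next sentence).** "For each outcome measure, change will be calculated as follow-up (at both 12 and 24 weeks) minus baseline and presented alongside 95% CIs".
- **Effect size (Data analysis).** Cohen's d is computed for each measure at 12 and 24 weeks, "using the following formula: (mean post-test − mean baseline)/(baseline standard deviation" (closing bracket cut from the quote). The men entering each mean are not named.
- **Expected loss (Sample size calculation).** "We aim to recruit 30 patients to the study which is standard practice for feasibility trials", and then "Assuming an 80% adherence rate, 25 patients should complete the intervention and subsequent evaluation".
- **Use (Data analysis).** "Preliminary feasibility results will inform the future RCT sample size calculation".

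Two passages limit the weight of these analyses. Secondary endpoints says the measures serve mainly to test whether they can be completed, although it also wants an indication of efficacy from them. Progression criteria attaches no threshold to the data-collection objectives.

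**The concern.** The ANOVA is a stated choice of method, not a detail left open. In its classical form it needs a complete row per man. Week 12 is the end of the intervention, so a man who finishes the programme but misses week 24 drops out of the ANOVA's week-12 comparison even though his week-12 result was recorded. The protocol foresees this kind of loss.

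The d formula raises a separate question. A difference of two means equals the mean within-man change only if the same men are in both. If they are not, part of d reflects who stayed rather than how anyone changed.

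At stake are the precision of the 12-week estimate, and possibly its bias, together with the effect sizes carried into planning of the randomised trial.

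**Working it through.** **1. The plan's own figure.** 30 × 0.80 = 24, against the stated 25 (25/30 = 83.3%). The two agree within rounding. Either way, 5 to 6 of 30 men are expected to be incomplete.

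**2. Men kept by the ANOVA.** If 20% are lost overall, 24 to 25 of 30 remain. If instead 20% were missing independently at each follow-up (an assumption), 30 × 0.8 × 0.8 = 19.2, about 19, would remain.

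**3. Precision at week 12.** Suppose all 30 men are seen at week 12 and the losses come later. The standard error of the week-12 change then grows by √(30/25) = 1.095 or √(30/24) = 1.118, that is by 10 to 12%. Nothing else is lost if leaving is unrelated to outcome.

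**4. Bias in d under assumed dropout.** The documents give no dropout mechanism, so these inputs are assumptions: standardised scores with equal SDs, baseline to follow-up correlation ρ of 0.5 or 0.7, one follow-up visit, 20% loss, and log-odds of loss falling by 1 per SD of the score that drives it. Each scenario used 400,000 simulated men with a true change of 0. Complete-case values are divided by the completers' baseline SD.

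| What drives loss | Unmatched means | Complete cases | Regression on baseline, all men |
|---|---|---|---|
| Nothing (ρ 0.5 / 0.7) | 0.00 / 0.00 | 0.00 / 0.00 | 0.00 / 0.00 |
| Poor baseline score | +0.085 / +0.120 | -0.093 / -0.055 | 0.00 / 0.00 |
| Poor follow-up score | +0.174 / +0.176 | +0.087 / +0.054 | +0.134 / +0.095 |

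A check by formula: let m be the amount by which the stayers' mean on the driving score exceeds the mean of all men, here about 0.175. When the follow-up score drives loss, the unmatched difference is m and the complete-case difference is (1 - ρ)m. That gives 0.5 × 0.174 = 0.087 and 0.3 × 0.176 = 0.053, in line with the table. When the baseline score drives loss, the complete-case difference is -(1 - ρ)m, so the sign reverses through regression to the mean.

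**5. Where the ANOVA is avoidably worse.** Suppose the driving score is the week-12 score and it was recorded before the man left. The ANOVA discards it, and its week-12 change is off by (1 - ρ)m, about +0.05 to +0.09. An analysis that keeps every week-12 value has no such error at week 12.

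**6. Unmatched d when nobody changes.** Let a fraction f leave whose baseline was δ within-group SDs worse. Then d = fδ / √(1 + f(1 - f)δ²). With f = 0.2:

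- δ = 0.5: 0.10 / √1.04 = 0.098
- δ = 1.0: 0.20 / √1.16 = 0.186

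The second value is just under the protocol's threshold of 0.20 for a small effect.

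**7. What this could do to trial planning (illustration only).** Assume a true d of 0.50, carried directly into a two-arm trial with two-sided 5% significance and 80% power. Then n per arm = 2(1.96 + 0.8416)²/d² = 15.70/d².

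- True d, 0.50: 63 per arm.
- Unmatched, 0.50 + 0.085 = 0.585 to 0.50 + 0.176 = 0.676: 46 down to 35 per arm.
- Complete cases, 0.50 - 0.093 = 0.407 to 0.50 + 0.087 = 0.587: 95 down to 46 per arm.

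**The case against.** The strongest reply has five parts.

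- **The change scores are separate from the ANOVA.** The sentence after the one naming the ANOVA promises a change at each follow-up with a 95% CI. A man seen at week 12 only can contribute to that. This stands: the loss of week-12 data applies to the ANOVA, not necessarily to the reported week-12 change.
- **Unmatched means are only one reading of the formula.** The formula follows directly on the change scores, so using the same men in both means is a natural reading, and analysis sets may be defined in a document not shown. This stands as to what is planned. The printed formula nevertheless permits both readings, and they differ by enough to matter.
- **The bias is assumed.** A reader might infer that the results will favour the fitter men who stay. The documents do not support that. They mention poor retention in the Discussion but do not tie it to worsening, and for complete cases the direction depends on the mechanism.
- **The consequence is small.** A complete-case bias of at most about 0.09 SD is modest in a single-arm study of 30 men whose secondary measures are mainly about completion. This stands and limits the weight of the point.
- **A mixed model is no cure-all.** When loss depended on the unseen follow-up score, regression using all men was off by +0.10 to +0.13, more than complete cases at +0.05 to +0.09. That regression is not the full mixed model, but it shows that using all men does not guarantee less bias.

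A reader might also infer that skeletal events and opiate use are to be analysed by a mean-change ANOVA. The sentence concerns measures that are scored, and skeletal events come from clinics and medical records without a score, so that reading goes too far.

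**Conclusion.** The point holds in a limited form. The protocol names a method that, in its classical form, throws away recorded data from men it expects to lose. The certain cost, for any man seen at week 12 but not at week 24, is precision: about 10 to 12% on the week-12 standard error if 5 or 6 men are lost after that visit. Bias is possible, not established. Under the assumed mechanisms with 20% loss, complete-case d is off by about -0.09 to +0.09, and by zero if loss is unrelated to outcome. The d formula is ambiguous; if read with unmatched means, it is inflated by roughly 0.1 to 0.2 when less fit men leave.

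The effect falls on secondary estimates that feed the randomised trial's sample size. Progression rests on recruitment and adherence and is untouched.

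**What to change.** In the Data analysis section or the analysis plan:

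1. Replace the ANOVA for the scored measures with a linear mixed model for repeated measures: visit as a categorical fixed effect, unstructured covariance, REML with Kenward-Roger degrees of freedom, including every man with any measurement.
2. Report model-based changes at 12 and 24 weeks with 95% CIs, and the number of men contributing at each visit.
3. Use the model-based change as the numerator of d, or else the mean within-man change among men with both values. State which men supply the baseline SD.

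The cost is a few sentences and a few lines of code; no new data are needed. The model assumes that missingness depends only on observed data and does not remove bias when loss depends on unseen scores. Effect sizes passed to trial planning should carry that caveat.
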